#### Control group

A waiting list control group will be used. They will be assessed at baseline and endline (5 weeks from the date of baseline assessment). They will receive the intervention after the intervention is complete in the intervention group.

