**Methods:** The project will be carried out in Bungoma and Kitale towns in Western Kenya, among youths (18-29 years) visiting selected barber shops for a routine haircut. The project will collaborate with local musicians to produce mental health-themed music to be played in selected barber shops. Selected barbers will be trained as facilitators in the delivery of doing what matters in times of stress (DWM). The barbers will use MH-themed music to initiate discussion on the project with youths visiting their barbershops. Those who consent will be screened for eligibility by research assistants, and eligible ones will be enrolled in the project by the barber. The barbers will help deliver the DWM intervention, which will last five weeks for each participant. Thereafter, selected participants will receive entrepreneurship and life skills training and support. A mixed-method approach involving a cluster randomized control trial design with each barber used as a cluster (40 clusters with 15 youths each); hence, a total of 600 youths (300 cases and 300 controls) and qualitative evaluation will be used for the evaluation. The 40 clusters will be randomised to either the intervention or control group using a randomisation ratio of 1:1. The project outcomes; depression, anxiety, stress, self-identified problems, resilience, functioning and mental health awareness will be assessed at baseline and post-intervention.

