## Methods and materials

### Study design

A mixed-method study approach will be used with both quantitative and qualitative study designs. For the quantitative part, the project will utilise a two-arm, cluster randomised control trial design with an intervention and waiting list control group, with two outcomes assessment points: preintervention and post-intervention, which will be done after the five-week intervention. The qualitative design will mainly be used for process evaluation to gather in-depth information regarding the role of music in the project, understand participants' knowledge and attitude towards mental health, and assess the participants' engagement and satisfaction with the project.

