#### Music development

MHPSS experts, youths, and local musicians will collaborate to develop mental health-themed music messaging that is appropriate for the targeted youths and provides essential mental health awareness. The contracted musicians will then use the messages to compose the songs. The music will be pre-tested and validated with selected youth and refined based on feedback.

After pre-testing and validation, four local hip-hop musicians will be engaged and facilitated to produce four mental health-themed music (1 per musician) in local languages. This music will be routinely played in select barber shops in 2 counties of Kenya where the project will be conducted.

The focus of these songs will be on mental health awareness, internalized stigma and experienced discrimination. The songs will be used by the barber to create an open discussion with the youth client and awareness of mental health and mental health stigma reduction. The barbers will use these songs to initiate a conversation about the project with eligible youths visiting their shops. Those willing to participate will be recruited by the barber and referred to the study research assistant, who will carry out screening and project pre-assessment. Those found eligible will be recruited and included in the project after consenting. Those found to have severe mental health conditions will be referred to public health facilities or related projects offering services for severe mental health conditions for diagnosis and management.

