### Blinding

Single blinding will be applied with only the data collectors/outcome assessors and the biostatistician analysing the data blinded of the participant's/barbers group allocation. Due to the nature of the intervention, it is not possible to blind participants and the barbers delivering the intervention.

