### Intervention procedure

We will train the barbers on basic mental health information, helping skills and regarding the DWM intervention. We will use the trained barbers as helpers to deliver the DWM intervention. Doing What Matters in Times of Stress intervention booklets and audio developed by WHO (WHO, 2020) will be used by the trained barbers as intervention material.

The trained barbers will meet the participants in three meetings:

**Introductory Appointment:** this will cover an introduction to the stress management guide, a discussion of interest, assessment, and planning. This session will take up to one hour.

**One-week follow-up:** This will cover using the stress management guide and support with overcoming barriers or problems with use and clarifying concepts. This will take upto 50 minutes.

**One-month follow-up:** This last session will cover the use of the DWM stress management guide, support overcoming barriers or problems with use, planning for continued future use, and completing follow-up assessment and goodbye or referral. This will also take approximately one hour. After the meetings, the youths in the intervention will be expected to engage with the provided intervention audio and illustration guides on their own. In case of any difficulties, they will be free to contact and engage the trained barbers to explanation and help in understanding the content. The intervention supported by the barber will last for five weeks for each participant, after which the Research

Assistants will conduct a post-intervention assessment. The intervention will be delivered in English.

The project will run a small validation exercise to verify understanding and develop a catalogue for words used in the local vernacular language that may not be well understood if spoken in English. The barbers will be trained always to ensure the participants understand the content. A word catalogue will be written to help each barber use the correct idioms based on the vernacular of the participants.

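### Endline is counted from the baseline date in controls but from the end of the five-week course in the intervention arm, so any delay in starting lengthens follow-up in that arm only

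*Protocol*

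**What the plan says.** All references are to the protocol.

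- **Control arm (Control group):** "They will be assessed at baseline and endline (5 weeks from the date of baseline assessment". The clock starts at baseline.
- **Design (Study design):** the two assessment points are "preintervention and post-intervention, which will be done after the five-week intervention". No interval from baseline is given.
- **Intervention arm (Intervention procedure):** "The intervention supported by the barber will last for five weeks for each participant", and the research assistants then carry out the post-intervention assessment. The clock runs from the course, not from baseline. The Abstract gives the same five-week duration.
- **Order of events (Music development):** interested youths are "referred to the study research assistant, who will carry out screening and project pre-assessment", and those found eligible are included afterwards. Baseline therefore comes before the introductory appointment. The gap between the two is not stated.
- **Last barber meeting (Intervention procedure):** the one-month session covers "planning for continued future use, and completing follow-up assessment and goodbye or referral". How this assessment relates to the research assistants' endline is not explained.
- **Model (Data analysis):** a linear mixed model adjusts for baseline scores and for sociodemographic variables that differ between arms. It names no term for time since baseline.

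**The concern.** A randomised comparison of endline scores assumes that both arms have been followed for the same time. Here the control interval is fixed at five weeks from baseline. The intervention interval is five weeks plus whatever passes between baseline and the first barber appointment. Because the pre-assessment comes first, that extra time cannot be negative.

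Participants enter with mild to moderate symptoms (PHQ-9 from 5 to below 15) and impaired functioning (WHODAS of at least 17). If some of them go on recovering without treatment after week five, the arm measured later shows more of that recovery, and the analysis attributes it to the intervention. This would touch every outcome, and a larger sample would not reduce it. Adjusting for elapsed time afterwards would repair it poorly: controls are all scheduled at five weeks, so a longer interval is nearly the same thing as being in the intervention arm.

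**Working it through.** **1. The plan's own figure.** The only timing figure is five weeks. Applied as written:

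- control endline = baseline + 5 weeks
- intervention endline = baseline + start lag + 5 weeks, plus any delay in the visit

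Visit delay can occur in either arm, since neither has a window. The start lag is what the rules add to one arm only. It is zero or more, and no section caps it.

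**2. Is a zero lag plausible?** It needs the introductory appointment to fall on the baseline day. Recruitment takes place in the barbershop, so that is possible. But youths come for a routine haircut, the baseline interview takes about 30 minutes, and the introductory session takes up to an hour with a working barber. Only one barber per shop is recruited, so that the shop can keep running normally. Nothing requires a same-day start.

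**3. Standard error of the treatment effect.** Inputs from Sample size: 40 clusters of 15, 20% attrition, intraclass correlation 0.02, baseline-endpoint correlation 0.5.

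- Completers per cluster: 15 × 0.8 = 12; per arm: 20 × 12 = 240
- Design effect: 1 + (12 − 1) × 0.02 = 1.22
- Variance factor for baseline adjustment: 1 − 0.5² = 0.75
- SE = √(2 × 1.22 × 0.75 / 240) = 0.087 SD

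**4. Bias and type I error.** Bias = lag (weeks) × recovery rate (SD per week). Two-sided rejection rate under no true effect = Φ(−1.96 + bias/SE) + Φ(−1.96 − bias/SE), a normal approximation. Both lag and recovery rate are assumptions. Each cell gives the bias in SD and, in brackets, the rejection rate.

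| Recovery per week | Lag 0 | Half a week | 1 week | 2 weeks |
|---|---|---|---|---|
| 0.02 SD | 0 (5.0%) | 0.01 (5.2%) | 0.02 (5.6%) | 0.04 (7.4%) |
| 0.05 SD | 0 (5.0%) | 0.025 (5.9%) | 0.05 (8.8%) | 0.10 (20.9%) |
| 0.10 SD | 0 (5.0%) | 0.05 (8.8%) | 0.10 (20.9%) | 0.20 (62.9%) |

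A three-day lag at 0.05 SD per week gives 3/7 × 0.05 = 0.02 SD.

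**5. Against the planned effect of d = 0.40.** 0.02 SD is 5% of it, 0.05 SD is 12.5% and 0.20 SD is 50%.

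**6. After the change.** With one anchor and one window in both arms, the scheduled difference in follow-up is 0 weeks, the timing bias is 0 SD and the type I error is 5%. The sample size is unaffected.

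**The case against.** The strongest reply is that equal timing was intended. The same five weeks appears throughout, Study design gives one pair of assessment points for both arms, and the Control group sentence may simply apply that interval to an arm with no course to finish. With a same-day or next-day start the difference is negligible. This stands as far as size goes. It does not remove the defect: the two rules name different events, and the difference can run one way only.

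Four stronger readings are tempting, and the protocol does not support them.

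- **That intervention youths are in fact assessed later.** No lag is given anywhere. The text supports only at least as late, and later with any lag.
- **That endline moves with every postponed meeting, or that youths who stop attending have no endline date.** Intervention procedure fixes the duration of support in calendar time, so start plus five weeks is a fair reading and gives everyone a date. The last meeting, at one month, also leaves some slack before week five.
- **That the barber's assessment at the last meeting undermines blinded outcome collection.** Blinding says "Single blinding will be applied with only the data collectors/outcome assessors and the biostatistician analysing the data blinded". Intervention procedure and Quantitative data collection give the endline and the data collection to research assistants. Nothing says that the barber's assessment supplies trial data.
- **That the fall expected from selecting on raised scores becomes bias.** Regression to the mean appears on re-measurement in both arms and does not grow in proportion to extra days. Only true recovery in the additional time counts.

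**Conclusion.** The point holds in conditional form. The endline rules use different starting events and allow longer follow-up in the intervention arm only, with no cap on the start lag and no adjustment for it. If distress eases with time, the error favours the intervention.

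Its size cannot be fixed from the protocol. It is nil with a same-day start and an endline at week five, and about 0.02 SD for a lag of a few days or slow recovery. It reaches 0.05 to 0.20 SD, with type I error of about 9% to 63%, only under the assumed 1 to 2 week lag and recovery of 0.05 to 0.10 SD per week. The 63% needs both upper assumptions at once and is not a forecast. I rate the point moderate: possibly negligible in practice, but one-directional, hard to repair after data collection and cheap to prevent.

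**What to change.** State one endline rule for both arms:

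- Count endline from the same event, for example the date of the baseline assessment, with one common visit window long enough to cover the course.
- Carry out the visit whether or not the barber sessions are finished.
- Record the actual baseline-to-endline interval and report it by arm.

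As a minor clarification, add a sentence saying that the assessment within the one-month barber session is not the trial endline.

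The cost is some wording and a scheduling rule, with no change in sample size. The downside is that some intervention youths will be measured before a delayed last session, so the estimate will include incomplete courses. That fits the intention-to-treat analysis already planned.

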### Study outcomes and outcomes measures

The effectiveness of DWM in reducing psychological distress is the primary aim and will involve the following outcome measures.

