#### ii) **Stress, anxiety, depression and personally identified problems**

We will use Generalized Anxiety Disorder 7-item (GAD-7) for anxiety assessment, Patient Health Questionnaire-9 (PHQ-9) for depression and Perceived Stress Scale (PSS-9) for stress. In a study among adolescents and young people (AYP) in Nairobi and Kiambu counties in Kenya, both the PHQ-8 ( $\alpha = 0.78$ ) and GAD-7 ( $\alpha = 0.82$ ) showed good internal consistency and goodness of fit (Osborn et al., 2021).

The GAD-7 has been used and has met psychometric standards in prior studies with Kenyan adolescents (Osborn et al., 2020; Osborn et al., 2021). Cronbach  $\alpha$  was 0.82 in a Kenyan adolescent sample (Osborn et al., 2020).

We will assess personally identified problems using the Psychological Outcome Profile (PSYCHLOPS), a sensitive measure of change in participants' identified problems after intervention with high internal reliability (Ashworth et al., 2009).

The secondary outcome will be the effectiveness of the intervention in improving functioning and resilience and will involve the following outcome measures.

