### Data analysis

The collected quantitative data in the Kobotool box will be imported into the Statistical Package for Social Sciences (SPSS) Version 27.0, where it will be coded and ready for analysis. Both per protocol and Intention to treat analysis (ITT) will be used in the analysis.

For descriptive analysis, mean and standard deviation or median and corresponding interquartile range will be used for continuous variables such as age, scores on depression, anxiety, stress, WHODAS, and BRS scales. For categorical variables such as gender and level of education, frequencies and percentages will be used to describe them.

To compare baseline characteristics between the intervention and control groups,  $\chi^2$  tests for comparison of frequencies and independent-sample t-tests for comparison of mean scores on normally distributed continuous measures or the Mann-Whitney U-test for comparison of the median for skewed continuous variables will be used.

The possible impact of missing data will be examined via sensitivity analyses of augmented data sets, and missing data will be handled through modern imputation techniques such as multiple imputation.

A mixed-effect linear model will be used to determine the effectiveness of the intervention, controlling for participants' sociodemographic characteristics found to be significantly different between the two groups, and the pre-assessment outcome scores.

The significance level based on a two-sided will be taken as  $P < 0.05$  at 95% confidence intervals.

For mental health outcome measures, we will also use the Reliable Change Index (RCI) and Clinically Significant Change (CSC) approaches, classifying participants as 'recovered' or 'improved', 'unchanged' and 'deteriorated' for each outcome (Jacobson & Truax, 1991). These approaches comprise measures of whether the change in scores is larger than expected due to outcome measure reliability and whether participants shift from clinical to non-clinical.

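### Four unranked scores carry the primary aim, each at two-sided 0.05 with no lead score, adjustment or success rule; if any one suffices, the false-positive rate is about 9-19% (about 5-10% for benefit, against 2.5%)

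*Protocol*

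**What the plan says.** All references are to the protocol.

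- **Study outcomes and outcomes measures** sets one primary aim: "The effectiveness of DWM in reducing psychological distress is the primary aim and will involve the following outcome measures".
- **Stress, anxiety, depression and personally identified problems** lists the measures for that aim. Three come in one sentence: "We will use Generalized Anxiety Disorder 7-item (GAD-7) for anxiety assessment, Patient Health Questionnaire-9 (PHQ-9) for depression and Perceived Stress Scale (PSS-9) for stress". The fourth follows: "We will assess personally identified problems using the Psychological Outcome Profile (PSYCHLOPS". The text then draws the line below them: "The secondary outcome will be the effectiveness of the intervention in improving functioning and resilience". So four scores sit on the primary side, and no order is given among them.
- **Data analysis** names the model, "A mixed-effect linear model will be used to determine the effectiveness of the intervention", and one general level: "The significance level based on a two-sided will be taken as $P < 0.05$ at 95% confidence intervals". On analysis sets it says: "Both per protocol and Intention to treat analysis (ITT) will be used in the analysis". It does not say which set carries the conclusion.
- **Sample size** uses one two-tailed alpha of 0.05, power 0.8, d = 0.40, a baseline-endpoint correlation of 0.5, ICC 0.02 and 20% attrition. It does not link these to any one score.

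**The concern.** A trial with one primary aim and four scores needs a rule that turns four P values into one conclusion. The protocol gives none: no lead score, no requirement that all four succeed, no hierarchy and no adjusted level. As written, a report could describe the primary aim as met because one score of four fell below 0.05, and nothing in the protocol would contradict it. Under that reading the error rate for the headline conclusion exceeds the 0.05 on which the trial was sized. Having two analysis sets without a stated priority leaves a second, smaller opening of the same kind.

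**Working it through.** **Inputs from the protocol.** Four primary scores; two-sided 0.05; 40 clusters of 15 (20 per arm); ICC 0.02; 20% attrition, so 12 completers per cluster; r = 0.5; d = 0.40.

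**Assumptions not in the protocol.** One significant score counts as success. The four test statistics are equally correlated at rho, shown from 0 to 0.9. There is no true effect on any score.

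**1. The plan's own sample size.** n per arm = 2(1.96 + 0.842)² × (1 − 0.5²) / 0.40² = 73.6, so 74. Design effect 1 + 14 × 0.02 = 1.28 gives 94.7, so 95. Dividing by 0.8 gives 119 per arm, about 238 in total, against the stated 600. The stated figure is not reproduced. That is a separate matter; its relevance here is that the planned 600 leave room for a stricter test.

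**2. Error rate, one analysis set, independent scores.**
- Either direction: 1 − 0.95⁴ = 0.185.
- Benefit only: 1 − 0.975⁴ = 0.096, against 0.025 for a single score.

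**3. Error rate with correlated scores.** Write each statistic as Z = √rho × g + √(1 − rho) × e, with g shared and e separate for each score. The chance that any of four exceeds 1.96 is one minus the average over g of the fourth power of the chance that one score does not.

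| rho | Either direction | Benefit only |
|---|---|---|
| 0 | 18.5% | 9.6% |
| 0.3 | 17.4% | 8.7% |
| 0.5 | 15.6% | 7.8% |
| 0.7 | 13.0% | 6.5% |
| 0.8 | 11.4% | 5.7% |
| 0.9 | 9.4% | 4.7% |
| One test | 5% | 2.5% |

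**4. Adding per protocol as a second chance.** Assume the per-protocol set is an 80% subset of ITT, so that the two statistics for one score correlate at √0.8 = 0.894. Simulation (1,000,000 draws) gives about 25%, 21%, 18% and 13% in either direction at rho 0, 0.5, 0.7 and 0.9. For benefit only it gives about 13%, 11%, 9% and 6.5%.

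**5. Can the planned size carry a correction?** Holm's strictest step is 0.05/4 = 0.0125.
- With 12 completers per cluster the design effect is 1 + 11 × 0.02 = 1.22, so the effective n per arm is 240/1.22 = 196.7.
- The standard error of d is √(1 − r²) × √(2/196.7) = 0.0873 with r = 0.5, and 0.1008 with r = 0.
- With 38 degrees of freedom, power for d = 0.40 at 0.0125 is 97.1% (r = 0.5) or 90.4% (r = 0).
- The effect detectable with 80% power rises from 0.251 to 0.304 SD (r = 0.5), or from 0.290 to 0.351 SD (r = 0).

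**6. Error rate after correction.** With all four scores null, a first step at 0.0125 gives 1 − 0.9875⁴ = 4.9% for independent scores, and about 4.3% at rho 0.5 and 3.7% at 0.7. For benefit only the independent case is 1 − 0.99375⁴ = 2.5%.

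**The case against.** **No success rule is stated.** A reader might infer that the protocol declares success on any one score. It does not. It gives a general significance level, and the four scores could simply be reported one by one. If all four had to succeed, there would be no inflation. This stands, and it is why every figure above is conditional. But the protocol does not require all four either, and that open choice is the defect.

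**13-19% is not the rate of false claims of benefit.** A reader might take the upper part of the table as the chance of wrongly concluding that DWM reduces distress. Those figures count false results in both directions. The rate for benefit over the same correlations (0.7 to 0) is 6.5-9.6%, and its comparator is 2.5%, not 5%. The lower end also depends on a correlation that the protocol does not give; beyond 0.7 both rates are lower still.

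**Eight chances.** Four scores in two sets might be read as eight tests of equal weight. The sets overlap heavily, so the second adds much less than four new tests would. The protocol says only that both analyses will be used, which fits a supportive per-protocol analysis. This part of the point is therefore secondary.

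**The SAP may settle it.** Adjustment methods and the ranking of analysis sets are often left to the SAP, which is not at hand. That weakens the point on analysis sets most. It does not remove the main point, because the protocol itself defines a four-score primary aim and itself fixes an unadjusted level.

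**The list may be incomplete.** The heading above the four scores is numbered ii) with no i) before it. This may be a numbering slip or lost text. The lists of instruments under Intervention and Quantitative data collection show no further distress scale, so there is no basis for counting a fifth score.

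**Conclusion.** The point holds in a limited form. Four unranked scores serve one primary aim at a flat two-sided 0.05, with no lead score, adjustment or success rule, while the sample size assumes one test at that level. If one significant score is taken as success in a single analysis set, the chance of at least one false significant result runs from 18.5% (independent scores) through about 13% (correlation 0.7) to about 9% (0.9). For a false finding of benefit it runs from 9.6% through 6.5% to 4.7%, roughly two to four times the 2.5% of a single test (4.7/2.5 = 1.9; 9.6/2.5 = 3.9). An unranked per-protocol analysis can raise this further. The documents do not show that the sponsor intends a one-of-four rule, nor do they give the correlations. They leave the rule open for the trial's main conclusion, and that should be closed.

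**What to change.** In the outcomes and Data analysis sections:

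1. State that the four primary scores will be tested in the ITT set with Holm's procedure at overall two-sided 0.05: the ordered P values are compared with 0.0125, 0.0167, 0.025 and 0.05, stopping at the first that fails. Alternatively, name one score as the single primary outcome and move the other three to secondary.
2. State that the per-protocol analysis is supportive only.
3. State that the primary aim will be claimed only for the scores that pass.

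Naming a single score is credible only if it is done before results by arm are seen. Holm over all four scores requires no choice among them.

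**Cost.** A few sentences. Under Holm the detectable effect at the strictest step rises by about 0.05-0.06 SD, from 0.25-0.29 to 0.30-0.35, still below the planned 0.40. Power for d = 0.40 at that step is 90-97% with the planned clusters and attrition, so no extra participants are needed. A single named primary outcome has no such cost, but the other three scores then cannot carry the primary claim.
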